### Secondary outcomes

Key secondary outcome variables are the individual components of the primary (death, severe ROP, BPD, NEC) and co-primary outcome variables (death, cognitive delay or language delay, motor impairment (GMFCS score of 2–5 [30]), as well as severe visual or hearing impairment,, the composite scores of the Bayley Scales (3rd edition), the rate of cerebral palsy (CP) according to the criteria defined by the European network ‘Surveillance of CP in Europe’, and the GMFCS score.

In addition to ‘severe ROP’ as component of the primary outcome, the ‘ROP Severity Score’ (also entitled ‘ROP activity and structure score’) [31] is assessed as secondary outcome, enabling better differentiation and likely being more relevant for functional outcome.

### Ethical considerations

The Helsinki Declaration shall be applied to the clinical trial, as well as Good Clinical Practice (GCP). The protocol was submitted and approved by the Ethics Committee of the University Hospital Tübingen as the lead ethics committee. Furthermore, the relevant ethics committees responsible for any of the participating study sites will have to approve participation of the site.

### Community engagement

A freely accessible web page for *FiO*_*2*_*-C* has been set up (www.fioc-study.eu), providing an overview of aims, partners, study outline, progress and milestones, meetings, findings and news.

### Form of consent

Written informed consent from parents or legal guardians is required for participation in the study.

### Insurance

Where required by national law, insurance will be obtained for all study patients.

### Sample size, power and study duration

The required sample size was calculated for the primary research hypothesis that the implementation of FiO_2_-C reduces the cumulative incidence of the composite primary outcome (death, severe ROP, BPD, or NEC).

The co-primary research hypothesis is that FiO_2_-C also reduces death or severe NDI (see outcome measures for details). These hypotheses are assessed as a-priori ordered hypotheses, where the co-primary hypothesis will only be tested in a confirmatory manner if the primary hypothesis has been confirmed. Consequently, no correction for multiple testing will be performed.

We assume that,
the cumulative incidence of the primary composite outcome of this study is 50% in the control groupFiO_2_-C reduces the burden of severe hypoxemia/hyperoxemia by 25–50% and (based on the assumption that (again) 25–50% of the outcome is associated with recurrent hypo−/hyperoxemia) effects a relative risk reduction in this outcome by at least 12.5%.

In summary, we assume a reduction in the primary outcome from 50% (in the control group) to 44% in the intervention group (FiO_2_-C).

Sample size calculations were based on a Χ^2^-test, assuming a power of 80% and a significance level of 5%. Based on these assumptions, 1110 infants are required in each treatment group (total 2220 infants). Because all components of this primary outcome will be determined during the initial hospitalization (i.e. until first discharge from neonatal care), the rate of drop-out before ascertainment of the primary outcome will be low as < 5%. Hence, a total of 2340 infants need to be enrolled and randomized (see Fig. 1).

**Fig. 1 Fig1:**
[figure not shown]
Anticipated Trial Flow

Assuming an incidence of 50% for the co-primary outcome in the control group and a relative risk reduction (RRR) of 25% for the co-primary outcome in the FiO_2_-C group, the proposed sample size will have a power > 80% to prove this difference even if up to 20% of randomized infants will be lost to follow-up until 24 months corrected age.

It is estimated that about 90% of all ELGANs will qualify for inclusion into this study without any exclusion criteria. Estimating a participation rate of 80%, approximately 3350 infants have to be screened.

We estimate a recruitment of about 65 patients per month and therefore the recruitment phase of the study will last for approximately 36 months. The individual participation in the study will be about 27 months (between 56 and 91 days of treatment – depending on GA at birth - with an additional follow up to 24 months corrected age).

### Data analysis

Analysis of the primary outcome will be based on the intention to treat analysis set, which comprises all randomized patients. Portions of infants with primary endpoint will be compared in a statistical model that accounts for the factors considered by the randomization procedure and the randomization of twins and other multiples. The treatment effect will be reported as a risk ratio and as a risk difference with 95% confidence interval. The co-primary outcome will be assessed only if superiority of FiO_2_-C with respect to the primary outcome is confirmed at the 2-sided level of 0.05. This hierarchical testing procedure maintains a multiple type I error of 0.05. All statistical analyses will be described in detail in a statistical analysis plan completed before closure of the database. An interim analysis for efficacy is not intended.

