**Methods:**

An outcome-assessor-blinded, randomized controlled, parallel-group trial was designed and powered to study the effect of FiO_2_-C (in addition to routine manual control (RMC) of FiO_2_), compared to RMC only, on death and severe complications related to hypoxemia and/or hyperoxemia. 2340 ELGANS with a GA of 23 + 0/7 to 27 + 6/7 weeks will be recruited in approximately 75 European tertiary care neonatal centers. Study participants are randomly assigned to RMC (control-group) or FiO_2_-C in addition to RMC (intervention-group). Central randomization is stratified for center, gender and PMA at birth (< 26 weeks and ≥ 26 weeks).

FiO_2_-C is provided by commercially available and CE-marked ventilators with an FiO_2_-C algorithm intended for use in newborn infants. The primary outcome variable (composite of death, severe ROP, BPD or NEC) is assessed at 36 weeks PMA (or, in case of ROP, until complete vascularization of the retina, respectively). The co-primary outcome variable (composite outcome of death, language/cognitive delay, motor impairment, severe visual impairment or hearing impairment) is assessed at 24 months corrected age.

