### Patients

#### Inclusion criteria

GA at birth 23 + 0/7 to 27 + 6/7 weeks

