### Randomization and allocation concealment

Study participants are randomly assigned in a 1:1 ratio to FiO_2_-C in addition to RMC of FiO_2_ (test intervention) or RMC of FiO_2_ only (control intervention).

A web-based randomization tool provided by the Interdisciplinary Center of Clinical Studies at the University Medical Center of the Johannes Gutenberg University Mainz is being used in this study. This program enables bound (into the same treatment group) or free (into different treatment groups) randomization of multiples based on parental choice and the number of available devices enabling FiO_2_-C.

A minimization algorithm is applied to preferentially aim for an even distribution of treatment assignment in both GA strata (i.e. < 26 weeks and ≥ 26 weeks; 1st priority) and both gender strata (2nd priority) within each center.

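### The primary model is tied to randomization factors that hold gestational age in two classes; adding the recorded age in days would gain a little precision (optional)

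*Protocol article*

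**What the plan says.** In the protocol article, the Data analysis section states that infants with the primary endpoint will be compared in "a statistical model that accounts for the factors considered by the randomization procedure", and that the model also allows for the randomization of twins and other multiples. The effect is to be reported as a risk ratio and a risk difference with 95% confidence intervals. The section names no model family and no coding of covariates. It leaves the detail to a statistical analysis plan (SAP) to be completed before database closure.

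The randomization factors are given in two places. The abstract's Methods paragraph says: "Central randomization is stratified for center, gender and PMA at birth (< 26 weeks and ≥ 26 weeks". The section on randomization and allocation concealment describes a minimization within each centre that aims for balance first in "both GA strata (i.e. < 26 weeks and ≥ 26 weeks; 1st priority", and then by sex.

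The inclusion criterion is "GA at birth 23 + 0/7 to 27 + 6/7 weeks", so GA must be established to the day before an infant can enter.

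**The concern.** If GA enters the model in the form used for randomization, an infant of 23+0 weeks is treated as having the same expected risk as one of 25+6, and 26+0 is treated like 27+6. The trial makes GA its first balancing priority, which suggests that the sponsor regards it as strongly prognostic. Coarsening such a covariate to two levels gives up part of the precision that adjustment could bring. Minimization on the two strata also leaves the age distribution within each stratum to chance, and a two-level term cannot adjust for that.

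What is at stake is power on the primary comparison. The design targets 80% for a six-point difference, and the co-primary outcome is tested in a confirmatory manner only if the primary hypothesis is confirmed.

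**Working it through.** **Inputs from the protocol article.** Risks of 50% and 44%, two-sided 5% level, 80% power, 1110 per group (2220), dropout below 5%, 2340 randomized.

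**The plan's own figure.** With p̄ = 0.47, n = [1.960·√(2·0.47·0.53) + 0.842·√(0.50·0.50 + 0.44·0.56)]² / 0.06² = 1086 per group, or 1119 with continuity correction. The stated 1110 lies between these. 2220/0.95 = 2337, against 2340. Power of the unadjusted comparison at 1110 per group is 80.9%. The sample size therefore reproduces, and it assumes no GA adjustment.

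**Inputs that are assumed.** The article gives neither risk by week nor an age distribution. Assumed here: a mix of 8/15/20/26/31% for weeks 23 to 27, and three pairs of end-point risks averaging about 50%: 70% to 39%, 82% to 32%, and 92% to 26%. Risks between the end points were interpolated on the logit scale and, as a variant, on a straight line.

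**Formulas.** With w the share and p the risk in each week, and m the mean risk:

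- R² = Σ w(p − m)² / [m(1 − m)], once with p averaged within the two strata and once by week.
- Residual variance ratio = (1 − R²_week)/(1 − R²_two-class).
- Equivalent extra infants = 2220 × (1/ratio − 1).
- Power = the two-proportion formula for 50% versus 44%, with 1110/(1 − R²) per group.

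**One row in full (82% to 32%, logit).** Weekly risks are 82.0, 72.1, 59.4, 45.4 and 32.0%, with mean 51.0%. The strata have risks of 68.0% (share 0.43) and 38.1% (share 0.57). Between-stratum variance is 0.43·0.1707² + 0.57·0.1288² = 0.0220, and between-week variance is 0.0278. Dividing each by 0.2499 gives R² of 8.8% and 11.1%. The ratio is 0.8888/0.9120 = 0.9745, and 2220 × (1/0.9745 − 1) = 58 infants. The effective group size rises from 1217 to 1249, and power from 84.3% to 85.2%.

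| Risk, week 23 to 27 | Interpolation | R² two-class | R² by week | Variance ratio | Extra infants | Power two-class → by week |
|---|---|---|---|---|---|---|
| 70% to 39% | logit | 3.1% | 4.1% | 0.990 | 21 | 82.1 → 82.5 |
| 70% to 39% | straight | 3.0% | 4.0% | 0.990 | 21 | 82.1 → 82.4 |
| 82% to 32% | logit | 8.8% | 11.1% | 0.974 | 58 | 84.3 → 85.2 |
| 82% to 32% | straight | 7.9% | 10.3% | 0.974 | 60 | 84.0 → 84.9 |
| 92% to 26% | logit | 17.4% | 21.4% | 0.952 | 112 | 87.7 → 89.2 |
| 92% to 26% | straight | 13.7% | 17.9% | 0.951 | 114 | 86.2 → 87.9 |

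From unrounded values, the power gain runs from 0.4 to 1.6 points.

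**Check with GA in days.** The table uses week-by-week risks, not a model in days. A separate calculation in days took a logit-linear gradient, overall risk of 47% and three other assumed age distributions. At odds ratios of 1.5 to 2.0 per week earlier, the standard error falls 0.9% to 3.0% relative to the two-class factor, worth about 38 to 141 infants. Over the wider span of 1.25 to 2.5, the range is about 12 to 233 infants and 0.2 to 2.7 points of power.

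**Simulation.** Standardized logistic regression was run 600 times with 2220 infants, fitting every model to the same data sets. The entries are empirical standard errors of the risk difference.

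| True risk | Unadjusted | Two-class | Linear days | Both |
|---|---|---|---|---|
| odds ratio 1.5 per week | 0.02186 | 0.02129 | 0.02105 | 0.02108 |
| odds ratio 2.0 per week | 0.02118 | 0.01932 | 0.01906 | 0.01909 |
| step at 26 weeks | 0.02143 | 0.02047 | 0.02065 | 0.02046 |

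When the gradient is smooth, adding days helps slightly. When risk is a true step at 26 weeks, days alone does slightly worse than the stratum, and using both loses nothing. None of these calculations includes centre, sex or the correlation within multiples.

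**The case against.** The strongest reply is that the article makes no error here. It sets out the adjustment in one sentence and defers the detail to a SAP that is not shown. Coding and functional form commonly belong there. A SAP that added GA in days beside the stratum would comply fully with the article. This stands: a reader might infer that the protocol confines GA to two classes, but the text excludes no further covariate and says nothing about coding. The point therefore concerns the literal reading of a stated choice and does not allege a contradiction.

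A reader might also infer that the planned estimate is biased by age imbalance within strata. The documents do not support that. Such imbalance is chance variation, already reflected in the confidence interval, and adjusting for the randomization factors is a valid primary analysis.

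The gain is also small. In the calculation in days, the two-class factor already captures about 70% to 77% of the variance that GA in days would explain, and every power figure in the table starts above the planned 80%. This stands as well, and is why the point is optional.

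Finally, replacing the stratum by a continuous term would not be safe. It would drop the first-priority minimization factor, for which the article says the model will account, and could lose a little precision if the form were wrong. That objection is met by adding the term and keeping the stratum.

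**Conclusion.** The point holds as an optional improvement. The article links the primary model to factors in which GA has two levels, while the exact value is available at baseline for every infant. Under the assumed mix and gradients, using it would lower residual variance by a further 1% to 5%, equivalent to about 20 to 115 infants on 2220 and about 0.4 to 1.6 points of power. These figures depend wholly on a risk gradient and an age distribution that the documents do not supply, and they move with both. Validity, type I error and the stated sample size are unaffected. The same reasoning may extend to the co-primary outcome, but no gain was computed for it and none should be quoted.

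**What to change.** Before database closure, pre-specify that the primary and co-primary models include GA at birth in days as a continuous term, for example a restricted cubic spline with the knots fixed in advance. It should come in addition to, not in place of, the two-level GA stratum, sex, centre and the multiples structure. Obtain the risk ratio and risk difference by standardizing the fitted risks over the analysed infants, which also avoids the convergence problems that direct risk-ratio or risk-difference models can have with a continuous covariate.

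The cost is a line or two of analysis-plan wording. No new data are needed, and the reported effect measures, significance level and sample size stay as they are. The one small burden is that the functional form has to be settled in advance.

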### Monitoring safety

An independent Data Monitoring Committee (DMC) is instituted and monitors recruitment, compliance, and safety parameters after 50, 100, 200 and 300 patients have completed 44 + 0/7 weeks PMA, and after every 200 patients have reached this age thereafter.

### Safety parameters

Safety parameters monitored by the DMC include:

Early deaths (for the DMC defined as < 44 weeks PMA), late deaths (for the DMC defined as ≥44 weeks PMA), all deaths, BPD, discharge on home oxygen or home positive pressure respiratory support, severe ROP, NEC, (focal) intestinal perforation requiring laparotomy, PDA requiring treatment, intraventricular hemorrhage >grade 2, cystic periventricular leukomalacia. Because the safety parameters include components of the primary outcome, the incidence rates and 95% confidence intervals, these parameters will be ‘coded’ as “safety parameter A-I”.

Furthermore, safety analyses include occurrence and rates of reported adverse events and incidents by treatment group.

#### Medical ethics committees

At the time of submission, the relevant ethics committee in Germany approved the study. Applications for approvals are currently underway in additional countries (e.g., the Netherlands and Switzerland).

#### National Regulatory/competent authorities

At the time of submission, the National Regulatory/Competent Authority of Germany (BfArM) approved the study. Authority approval may not be necessary elsewhere – but this will be determined in collaboration with the relevant ethics committees.

## Discussion

### Need for a trial

Oxygen is one of the drugs most frequently used in ELGANs and yet, our knowledge on the optimal level of oxygen in arterial blood (or in appropriate simplification the optimal target range for SpO_2_) and even optimal technology for monitoring oxygen levels is incomplete [32–34]. Short-term studies in preterm infants demonstrated that FiO_2_-C improved the time within the assigned SpO_2_ target range. In these studies, percent time within the assigned SpO_2_ target range increased by approximately 10% points to around 70–90% and the improvement was independent of the SpO_2_ target range, the FiO_2_-C algorithm, and the proportion of time spent within SpO_2_ target range in the control-group [21, 22, 35, 36]. It is, however, unclear if more time spent within the assigned SpO_2_ target range will also translate into positive long-lasting effects on clinically relevant outcomes. For example, despite higher proportions of time spent within the SpO_2_ target range, FiO_2_-C might on the one hand side reduce the amplitude of SpO_2_ fluctuations, but, at the same time increase the frequency of SpO_2_ oscillations and thereby might carry additional risks. This randomized controlled trial will ensure an appropriate assessment of safety and efficacy of FiO_2_-C, before it is implemented into standard care.

### Discussion of the study intervention period

The study intervention period was chosen because Di Fiore et al. showed that hypoxemic episodes evolve over the first 2 weeks of life and hence starting the intervention within 48 h after birth seems appropriate. This will enable a reasonable time frame to inform parents, even if birth of the infant occurs at night or on weekends, and to enable a meaningful parental decision on participation.

As described by Di Fiore et al. [5] and confirmed by Poets et al. [6], hypoxemic episodes occurring beyond the 4th week of life are more strongly associated with adverse long-term outcomes than hypoxemic episodes occurring within the first 4 weeks of life. Hence, the study intervention should not end at 32 weeks PMA. Infants with prolonged and frequent hypoxemic episodes beyond this age may benefit most from effective FiO_2_-C.

### Discussion of chosen population

Because diseases thought to be related to inappropriate use of oxygen such as ROP and BPD essentially only occur in ELGANs, an assessment of efficacy and safety of long-term application of FiO_2_-C can only be performed in this patient population.

### Discussion of chosen SpO_2_-target range

The NeOProM collaboration has shown that the higher SpO_2_-target range of 91 to 95% is associated with a decreased risk of early deaths at 18 to 24 months corrected age and NEC, but with an increased risk of ROP [11]. Furthermore, a post-hoc analysis of the BOOST-II data indicated that a higher proportion of time within the assigned target range could enhance this beneficial effect [37]. Consequently, in the FiO_2_-C trial the lower limit of the center-specific SpO_2_ target range has to be set to ≥87% SpO_2_.

## Trial status

Protocol version 4: April, 26th, 2018. Recruitment has started in July 2018 and is expected to be finalized in July 2021. The last patient out (after follow-up) will be expected in October 2023.

## Data Availability

Data sharing is not applicable to this article as no datasets were generated or analyzed for the current manuscript.

## Abbreviations

ASDII: Atrial Septal Defect II
BfArM - Federal Institute for Drugs and Medical Devices: Bundesinstitut für Arzneimittel und Medizinprodukte
BMBF - German Federal Ministry of Education and Research: Bundesministerium für Bildung und Forschung
BPD: Chronic lung disease of prematurity
CP: Cerebral palsy
eCRF: Electronical case report form
ELGANs: Extremely low gestational age neonates
FiO_2_-Controller / FiO_2_-C: Closed loop automated control of FiO_2_
GA: Gestational age
GMFCS: Gross Motor Function Classification System
NDI: Neurodevelopmental impairment
NEC: Necrotizing enterocolitis
paO_2_: Arterial oxygen partial pressures
PFO: Patent foramen ovale
PO_2_: Oxygen partial pressures
RMC: Routine manual control
ROP: Retinopathy of prematurity
RRR: Relative risk reduction
